### Overall study design

In order to use the CRR, the nursing homes will have to provide the medication list, the patient characteristics and the laboratory values for each patient in a digital format.

Taking into account the extra workload for the investigators, there will be a predefined day for each nursing home to send the files: nursing home A sends the files on Mondays, nursing home B sends the files on Tuesday, and so on.

All nursing homes will send the patient data both for control and intervention groups.

The randomisation will be performed by two of the authors ([name], [name]). The randomisation will be per main nursing home physician and stratified per ward. Physician A will be randomised in the control group and physician B on the intervention group, taking into account that the amount of patients in each group should be approximately the same.

#### Intervention group

The datasets will be screened through the CRR on a weekly basis. The messages delivered by the CRR will be sent via mail to the specific physicians. Each remark will be sent on a separate mail in a standardised way. In response to the report, the physician will send a feedback message within 36 h indicating, in a standardised way, whether:the advice was not followedthe advice was followedthe advice was changed.

After receiving this feedback, the investigators will process it in the CRR, in order to create the database for the study.

Additionally, regular care will be also applied. That is according to the Dutch Healthcare Inspectorate, a yearly medication review with a physician and a pharmacist, even though there is a substantial variation [25], For the centres included in this study there are no dedicated clinical pharmacist working in the nursing home.

#### Control group

In the control group patients will receive regular care (yearly medication review). In addition, these patients will also be screened using the CRR to obtain data that could serve for future evaluations within the project (for instance to compare how many advices would have been sent from the control group, the difference in remarks, etc.). However, this screening will be performed via a filter and the investigators will neither see nor evaluate any remark. These alerts will only be unblinded at the end of the study.

In addition, for both control and intervention group, the physicians will report any events including: hospital admission, specialist visit, emergency department visit, falls, delirium and death, via a questionnaire. This questionnaire will also include questions to know whether a medication review has been performed and how much time this medication review cost. Physicians will also report if there is any new patient. These electronic questionnaire will be sent by Google Drive via email weekly. At the end of the study, the physicians in the intervention group will receive a mail asking how much time, in average, they need to answer the remarks which are sent from the CRR. Figures 1 and 2.

**Fig. 1 Fig1:**
[figure not shown]
Schematic study design. *Other possible centres Amsterdam and Nijmegen

**Fig. 2 Fig2:**
[figure not shown]
Study schedule

### Endpoints

#### Primary endpoint

The primary outcome variable in this study is the proportion of patients with at least one of the events, including hospital referrals (i.e. referral to a specialist, emergency department visit and hospital admission), delirium, falls, and/or deaths. All these events will be reported by the nursing home physician via the electronic questionnaire. To this end the study will assess the differences between regular care (control group) and regular care + CRR (intervention group).

#### Secondary endpoints

As secondary endpoints, the same outcome variable will be used to analyse the possible differences between institutions, to separately analyse psychogeriatric and somatic wards, to analyse the medication related events, and to separately analyse each of the parameters included in the combined endpoint (hospital referrals, delirium, falls, and/or deaths).

In order to get this information, physicians will be asked to report any events including: hospital admission, polyclinic visit, emergency department visit, falls, delirium and death. These questions will be asked via an electronic questionnaire via Google Drive. The assessment of whether the event is or could be drug related or not will be done exclusively by the physician.

The quality of life will be measured using the EQ-5D questionnaire both for patients in the control group and patients in the intervention group. The questionnaire will be performed at the end of the study (i.e. after one year follow-up), both for psychogeriatric and somatic patients. The results will be compared between intervention and control group. For both patients groups a caregiver/nurse will answer the questionnaire.

In addition the analysis of the MAI and the cost evaluation will also be performed for both control and intervention group.

### Setting

Nursing homes in the Netherlands will be invited to participate in the study; these nursing homes should be able to deliver the medication data and the laboratory data electronically. In case the data would come from the hospital in the neighbourhood, this hospital would have to agree on providing the data. If a nursing home meets these requirements, it is eligible for participation in the present study.

### Population

Nursing home residents; the total study population is estimated to have a total of 3500–4500 patients. This wide range in amount of patients comes from the fact that patients will not be included singly but as complete nursing homes. In addition, enough patients should be included to ensure reliable results taking into account possible loss to follow up.

### Inclusion criteria

Residents living in a nursing home in the Netherlands.

The nursing homes are able to deliver the medication and lab data electronically.

### Randomisation, blinding and treatment allocation

#### Randomisation

per main nursing home physician. The randomisation will be stratified per ward (somatic and psychogeriatric). In case the physician would be absent the suitable option will be followed:

Absence ≤ 6 weeks intervention group: the mails with the messages obtained from the CRR will still be sent to the main physician. If the replacing physician would also participate in the study, he will not get any mails for the group of patients for which he/she is the replacing physician during this period. It is assumed that if the replacing physician is included in the intervention group, he could apply the mails from his own group to all patients. If the replacing physician is included in the control group, it is assumed that no interventions will be performed.

Absence > 6 weeks intervention group: the mails will be sent to the replacing physician; if the replacing physician would be one of the physicians already included and randomised in the control group, the replacing physician will get the mails only for the patients in the intervention group.

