Computerised clinical decision support systems (CCDSS) can be defined as decision-aiding tools which provide health care professionals with clinical knowledge and patient-related information, intelligently filtered or presented at appropriate times, so as to enhance patient care [21–23]. Within the SCREEN project (Supporting Clinical Rules in the Evaluation of Elderly patients with Neuropsychiatric disorders), a CCDSS named Clinical Rule Reporter (CRR) has been developed. This system currently analyzes, independently of the applied prescribing software, the medication used by patients in relation to their co-medication, the laboratory data (including renal function), and other relevant clinical data like diagnosis and comorbidities [24]. The CRR combines the clinical rules (algorithms) with the medication list, patient characteristics and laboratory values of the patients in order to obtain concrete advices. These clinical rules or algorithms work with triggers that identify drug related problems like renal or liver dysfunction as well as the need of new medication (stomach protection or laxative agents), the necessity to stop a certain drug or decrease the dose according to age, etc.

Due to the lack of evidence concerning the benefits of medication reviews performed in the nursing home setting, we propose a study aiming to demonstrate a positive effect that the CRR, as a health care intervention, may have on the target population. This population consists of older people (≥65 years) with a high risk of suffering harm when using inappropriate drugs. By this we mean people living in nursing home facilities; these people often suffer from polymedication among other risk factors such as multimorbidity, impaired cognition, renal dysfunction, and increased risk of falling.

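### During absences of up to 6 weeks the CRR mails go to the absent physician and are withheld even from an intervention-arm replacement, so delivery is late or lost and the effect estimate is pulled towards no difference

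*Protocol article*

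**What the plan says.** The protocol article, section Randomisation, has two rules for the absence of an intervention physician.

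- **6 weeks or less:** "the mails with the messages obtained from the CRR will still be sent to the main physician". If the replacement also takes part in the study, "he will not get any mails for the group of patients for which he/she is the replacing physician during this period". No exception is made for a replacement in the intervention arm. Two assumptions follow: "if the replacing physician is included in the intervention group, he could apply the mails from his own group to all patients", and "If the replacing physician is included in the control group, it is assumed that no interventions will be performed".
- **More than 6 weeks:** "Absence > 6 weeks intervention group: the mails will be sent to the replacing physician". This applies even when the replacement was randomised to control, in which case the mails are limited to the intervention patients.

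Two other places bear on this. The Intervention group section describes weekly screening with a separate mail for each remark, after which "the physician will send a feedback message within 36 h". The Background says how remarks arise: "The CRR combines the clinical rules (algorithms) with the medication list, patient characteristics and laboratory values of the patients".

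**The concern.** The tested intervention is regular care plus CRR over one year. Under the short-absence rule, the remarks on a resident go to someone who is not treating that resident at the time, while the physician who is treating the resident does not see them. Avoiding contamination is a reason to keep mails away from a control physician. It is no reason to keep them from a physician who already receives CRR mails for his or her own patients.

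Intervention residents stay in the intervention group for the whole year, so weeks with late or missing delivery pull the estimated difference towards zero. The sample size calculation allows for clustering and dropout but not for this. The feedback data (followed, not followed, changed) would also mix replies that are late or missing because of leave with replies that reflect judgement.

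**Working it through.** **1. The passages side by side**

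| Replacement, absence ≤ 6 weeks | Mails for covered patients | Protocol's assumption | Would sending them expose a control cluster? |
|---|---|---|---|
| Intervention arm | withheld | own mails could be applied to all patients | No |
| Control arm | withheld | no intervention | Yes |
| Not in the study | go to the absent physician; no separate rule | none stated | Only if he or she also covers control patients |

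The assumption in the first row conflicts in part with the Background. A remark triggered by one resident's renal function, drugs and age carries no information about another resident's. General prescribing awareness may carry over, but the patient-specific content cannot.

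The 36-hour reply is stated without exception in the Intervention group section, and the Randomisation section neither waives nor reassigns it during absence. A physician on leave would not normally meet it.

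**2. Reproducing the plan's sample size**

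Inputs from Sample size calculation: p1 = 0.20, p2 = 0.15, two-sided α = 0.05, power 80%, ICC = 0.01, m = 56, dropout 10%.

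- n = [1.96·√(2·p̄·(1−p̄)) + 0.842·√(p1(1−p1) + p2(1−p2))]² / (p1−p2)², with p̄ = 0.175. This gives 905.4, rounded up to **906** (stated: 906).
- DE = 1 + 55 × 0.01 = 1.55. Then 906 × 1.55 = 1404.3, rounded up to 1405, and 1405 / 0.90 rounded up is **1562** (stated: 1562).

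**3. Size of the dilution**

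The protocol gives no number of absence weeks. Assume w undelivered weeks per physician-year, with all benefit of those weeks lost and the effect proportional to delivered weeks:

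- absolute difference = 0.05 × (1 − w/52)
- effective n per group = N × 0.90 / 1.55, which is 907 for N = 1562, 1016 for N = 1750 and 1306 for N = 2250

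The values 1750 and 2250 are half of the planned 3500 and 4500 patients (Population; Time schedule).

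| w | Relative reduction | Power, 1562 per group | Power, 1750 | Power, 2250 |
|---|---|---|---|---|
| 0 | 25.0% | 80% | 84% | 92% |
| 3 | 23.6% | 75% | 80% | 89% |
| 5 | 22.6% | 71% | 76% | 86% |
| 8 | 21.2% | 65% | 70% | 81% |

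Example for w = 8: 0.05 × (1 − 8/52) = 0.0423, so the intervention proportion is 0.1577 and the relative reduction 0.0423 / 0.20 = 21.2%.

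**4. If only half of the effect in those weeks is lost**

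Replace w by w/2. Power for w = 3, 5 and 8 is then 78%, 76% and 73% at 1562 per group, and 82%, 80% and 78% at 1750.

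**The case against.** The strongest reply is that this is a disclosed design choice with a conservative bias. The mails stay with the randomised physician, the protocol says openly that no intervention is assumed under a control-arm replacement, and the rule cannot create a false benefit. Mails sent to the main physician are not discarded and can be acted on after return. Medication changes made before the absence need not be undone during it. The clinical rules are general, so some carry-over by an intervention-arm replacement is credible. The study also plans to enrol more than the calculated minimum.

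Most of this stands, and it limits the size of the problem. A reader might infer that intervention residents get regular care only in every week of short leave, that the 36-hour rule and the absence rule flatly contradict each other, or that power drops to 65%. The documents support none of these:

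- Delivery may be late rather than lost, and earlier changes may persist.
- The 36-hour reply is left unaddressed for absences. It is not contradicted in terms. Likewise, the carry-over assumption is incomplete rather than wholly false, and the protocol does not offer it as its reason for withholding the mails.
- The 65% figure needs 8 fully lost weeks at the minimum sample. At the planned size the same assumption gives 70%–81%.

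The reply does not explain why an intervention-arm replacement should be denied mails when no control cluster would be exposed. The longer-absence rule sends mails even to control-arm replacements, so avoiding contamination is not applied consistently either.

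**Conclusion.** The point holds as a cheap improvement to the design. For absences of up to 6 weeks, the study's own mailing rule makes delivery late or incomplete, and the bias is towards no effect. The power figures above rest on an assumed 3 to 8 weeks of short absence per physician-year, no recovery of benefit, and an effect proportional to delivered weeks. They are therefore close to an upper limit on the loss for those weeks. At the planned 1750 to 2250 per group the cost is about 3 to 14 percentage points of power (92% to 89% at 3 weeks and 2250 per group; 84% to 70% at 8 weeks and 1750 per group). It is less if alerts are acted on after return. Part of the loss would remain after the change below, because weeks covered by a control-arm replacement stay undelivered, and the protocol does not say how often that happens.

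**What to change.** In the Randomisation section, for absences of 6 weeks or less:

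1. Send the study mails for the absent physician's intervention patients to the replacement when that replacement is in the intervention arm. Send them to a replacement outside the study only if he or she covers no control patients.
2. Keep withholding them from control-arm replacements.
3. Delete the assumption that mails about one physician's patients can be applied to all patients.
4. Reconcile the absence rule with the 36-hour reply in the Intervention group section: state who replies, or how the missing reply is recorded.
5. Log the weeks without delivery for each physician, so that delivered exposure can be reported and absence can be told apart from judgement in the feedback data.

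The cost is a short amendment and a changed mail recipient during leave. The centre's contact person must report who is covering, and a replacement outside the study needs brief instruction on the standardised reply. Recruitment began in June 2013 and centres start at different times, so centres already running would have had different routing. The date of the change should be recorded for each centre. No control-arm physician would receive an alert during a short absence.

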#### Blinding

Blinded for patients; In addition, physicians will be emphatically requested not to talk about the emails.

#### Treatment allocation

If a patient dies or moves to another institution, the replacing patient will not take over the place in the study. Death is one of the endpoints for the study and so the study would be completed for that patient; moving to another institution will be considered as loss to follow-up. To account for these patients the physicians will have to report every time a new patient gets in the nursing home, in this way a filter can be applied to not analyse these new patients.

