### Sample size calculation

Calculation of the total number (one event per patient). The aim is to reduce the number of patients with at least one event with 25% by using the CRR compared to the regular care. These events consist of medication related hospital referrals, delirium, falls, and/or deaths.

In order to calculate the sample size a pilot study was performed. Nursing homes physicians from the region (Envida and Zuyderland) have informed, via an electronic questionnaire, about any hospital referrals, delirium and/or falls within their patients. In addition, they stated whether these events could be medication related. This pilot study has lasted for 5 months. No patient information was given.

The pilot study showed a proportion of patients with at least one event (combination of fall, delirium, hospital referral, and death) in the control group of 0.16 and a mean number of patients per physician of 56.

Assuming a proportion of patients with at least 1 event during 1 year follow-up of 0.20 in the control group, a 25% reduction by using the CRR compared to regular care, i.e. proportion reduces from 0.20 to 0.15, and a two-sided significance level (α) of 0.05, the number of patients per group required to detect an effect with 80% power equals 906. Accounting for the design effect (randomisation per physician; DE = 1 + (m-1)*ICC), where we assume an intra-class correlation coefficient (ICC) of 0.01, a mean number of patients per physician (m) of 56 (pilot study), and a 10% dropout rate, the required number of patients increases to 1562 per group.

We assumed a higher proportion of patients with at least one event in the control group (0.20) than the one found in the pilot study (0.16), because the number of falls were underreported in the pilot study and the follow-up duration is now longer, i.e. one year instead of five months.

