#### Primary study parameters

To detect a difference in proportions of the primary outcome (composite endpoint consisting of hospital referrals, delirium, falls, and/or deaths) between the groups (control versus intervention), logistic mixed effects analysis are applied with the following fixed factors: group (control or intervention), nursing home organisation (Envida, Zuyderland, Sevagram or Novicare), type of ward (psychogeriatric or somatic) and other variables related to the outcome, like age and sex.

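### Cohort membership rests on newcomer reports from physicians who know their arm, and the one-year yes/no model has no stated way to use the partial follow-up of residents who move

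*Protocol article*

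**What the plan says.** All references are to the protocol article.

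- **Newcomers.** Under Treatment allocation, "the replacing patient will not take over the place in the study". To put this into effect, "the physicians will have to report every time a new patient gets in the nursing home", and "in this way a filter can be applied to not analyse these new patients". No other route for identifying newcomers is named.
- **Leavers.** The same section separates two cases. For death, "Death is one of the endpoints for the study and so the study would be completed for that patient". For a transfer, "moving to another institution will be considered as loss to follow-up". It does not say whether an event recorded before the transfer still counts.
- **Outcome and model.** Primary endpoint defines a proportion of patients with at least one event, reported by the nursing home physician. Under Primary study parameters, "logistic mixed effects analysis are applied with the following fixed factors": group, organisation, type of ward, and covariates such as age and sex. No follow-up time or censoring is named. Time schedule sets one year per centre.
- **Who knows the arm.** Intervention group has the remarks mailed to the physician, who must answer each one. Study design calls physicians blinded; Blinding names only patients as blinded.
- **Data at hand.** Overall study design has every home send patient data for both arms. Control group says of the event reports, which cover both arms: "These electronic questionnaire will be sent by Google Drive via email weekly".
- **Planning.** Sample size calculation allows "a 10% dropout rate, the required number of patients increases to 1562 per group".

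**The concern.** Two features let the analysed data depend on what happens after randomisation.

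First, a newcomer is removed if the physician reports the arrival. An intervention physician cannot be blind while receiving and answering the remarks, and the same person reports the outcomes. If reporting is incomplete, residents with only part of a year at risk enter as if they had a full year, which lowers the observed event proportion. If completeness differs by arm, the comparison shifts.

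Second, a resident who transfers after some months has a partly observed year. A yes/no one-year model can only drop that resident, count the resident as event-free, or impute. If moving is linked to the outcome and also differs by arm, the choice matters. The trial is planned on a difference of 5 points (0.20 to 0.15), so an artefact of 1 or 2 points would be a substantial share of the effect sought.

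**Working it through.** **Step 1: the plan's own figures.** Inputs from Sample size calculation: 0.20 and 0.15, two-sided 0.05, 80% power, ICC 0.01, m = 56, dropout 10%.

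n = [1.960·√(2·0.175·0.825) + 0.8416·√(0.20·0.80 + 0.15·0.85)]² / 0.05² = 905.4, so 906, as stated. Design effect = 1 + 55·0.01 = 1.55. 906·1.55 = 1404.3; 1404.3/0.9 = 1560.3, so 1561 against 1562 stated, a rounding difference. The sample size is not in dispute.

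**Step 2: unreported newcomers, no true effect.** Assumptions (no figures in the documents): newcomers equal a fraction t of the starting cohort, a share u is unreported, and each has half a year at risk. Half-year risk = 1 − √0.80 = 0.1056. Observed proportion = (0.20 + t·u·0.1056)/(1 + t·u).

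- t = 0.2, u = 0.2 in the intervention arm and 0 in control: 0.2042/1.04 = 0.1964, a false benefit of 0.4 points. At t = 0.4: 0.7 points.
- u = 0.5 against 0: 0.9 points (t = 0.2) to 1.6 points (t = 0.4).
- u = 0.1 in both arms: no false difference, though both proportions fall slightly (0.198 at t = 0.2).

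**Step 3: movers.** Assumptions: constant event hazard λ = −ln(0.80) = 0.2231 per year; move hazard μ before a first event and kμ after it; μ set so that 10% move (μ = 0.105, 0.088, 0.076 for k = 1, 3, 5). Then:

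- no event, not moved: S = exp(−(λ+μ))
- moved without an event: M = μ/(λ+μ)·(1−S)
- event before any move: E = λ/(λ+μ)·(1−S)
- event and still resident at one year: R = λ·exp(−kμ)·(1−exp(−(λ+μ−kμ)))/(λ+μ−kμ)

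Three ways to handle movers: (A) exclude all, R/(R+S); (B) count earlier events and treat other movers as event-free, E; (C) count earlier events and drop other movers, E/(1−M).

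| Result | Rule | k = 1 | k = 3 | k = 5 |
|---|---|---|---|---|
| One-arm risk, true 0.200 | A | 0.200 | 0.186 | 0.176 |
| Odds ratio 0.15 v 0.20, same move hazards (true 0.706) | A | 0.706 | 0.707 | 0.707 |
| Same | B | 0.708 | 0.708 | 0.707 |
| Same | C | 0.706 | 0.706 | 0.706 |
| False difference, no true effect, one arm's move hazard doubled (points) | A | 0.0 | 1.3 | 2.0 |
| Same | B | 0.9 | 0.8 | 0.7 |
| Same | C | −0.9 | −0.8 | −0.7 |

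A positive difference means that the arm with more moving looks better. Simulating the same model gives up to 2.1 where the table shows 2.0.

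**Step 4: a cruder check on movers.** Fix the mover fractions directly, give movers 1 to 2 times the average risk, and assume no true effect. With 5% and 15% moving, the false difference is 0 to 2.5 points if movers are excluded and 2 to 4 points if all are counted as event-free. With 8% and 12% it is 0 to 1.0 and 0.8 to 1.6 points. With equal fractions it is zero.

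**The case against.** The strongest reply is that the article says very little here, and that more can be read into it than it contains.

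- **A reader might infer that movers are discarded along with their earlier events.** The text does not say so. It classes them as lost. A mover with a reported event already meets the endpoint definition, and the weekly report would be on file. This stands.
- **A reader might take the division by 0.9 as proof of discarding.** It is routine dropout inflation and says nothing about how movers are analysed. This stands.
- **A reader might see excluding newcomers as selection after randomisation.** It is the opposite: it protects the cohort present at the start. This stands, and only the reporting route remains open to criticism. Nor are physician reports the only possible source, since the patient files could reveal newcomers.
- **The fall in one-arm risk, to 0.176 at k = 5, is not bias in the treatment effect.** This stands: with equal move hazards the odds ratio is practically unchanged.
- **A hazard model need not replace the proportion.** It would change the quantity on which the trial is powered. Censoring at the move is also biased if frailty drives both moving and events; the model in Step 3 assumes that away. This stands against a new primary analysis, but not against a sensitivity analysis.
- **Component analyses.** Counting early deaths as no fall or no delirium gives the cumulative incidence with death as a competing event, a recognised quantity and not an error.

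Two things remain. Deciding cohort membership from reports by arm-aware outcome reporters is a choice the article makes, and a later analysis plan that relied on those reports alone could not recover newcomers who were never reported. And the named primary model has no place for a partial year.

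**Conclusion.** The point holds in a limited form. The cohort rule is right in intent but leans on the wrong source, when a better one is already collected. Its effect is about 0.4 to 1.6 points if 20% to 50% of newcomers go unreported in one arm only, and nil if reporting is equally complete in both.

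The handling of movers threatens the arm comparison mainly if moving differs by arm. With one arm's move hazard doubled and moving 3 or 5 times as likely after an event, the false difference is about 0.7 to 2 points if movers are excluded or those without an event are counted as event-free. With equal hazards the effect on the odds ratio is negligible.

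Every move, turnover and under-reporting rate used here is an assumption; the documents give none, and nothing in them shows that either process differs by arm. That intervention physicians know their arm is an inference from the mailed remarks. It is a safe one, but the Study design and Blinding sections describe physician blinding differently and should be reconciled. The stated sample size is unaffected.

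**What to change.** 1. Define the cohort as the residents listed in each centre's first data file, for both arms. Use physicians' newcomer reports only as a cross-check. This assumes that the first file lists every resident.
2. State that any event reported before a move counts as an event.
3. Keep the logistic mixed model as primary, and state one rule for movers without an earlier event. Steps 1 to 3 do not remove the problem entirely: in the doubled-hazard example, counting such movers as event-free or dropping them leaves 0.7 to 0.9 points, in opposite directions.
4. For that reason add a sensitivity analysis of time to first event by questionnaire week, censored at the move, with a physician random effect and the same fixed factors. Report the number of movers and the timing of moves by arm.

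The cost is a few sentences and a little programming, since the files and weekly reports are already collected. The downside is a second effect measure beside the proportion, and an analysis that itself assumes censoring at the move is unrelated to later risk given the covariates.
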